# Efficacy of extracranial stereotactic body radiation therapy (SBRT) added to standard treatment in patients with solid tumors (breast, prostate and non-small cell lung cancer) with up to 3 bone-only metastases: study protocol for a randomised phase III trial (STEREO-OS)

**DOI:** 10.1186/s12885-021-07828-2

**Published:** 2021-02-04

**Keywords:** MeSH: Oligometastases, Bone metastases, Stereotactic radiotherapy, Neoplasm metastasis, Radiosurgery, Lung neoplasms, Prostatic neoplasms, Breast neoplasms

## Abstract

**Background:**

Stereotactic Body Radiation Therapy (SBRT) is an innovative modality based on high precision planning and delivery. Cancer with bone metastases and oligometastases are associated with an intermediate or good prognosis. We assume that prolonged survival rates would be achieved if both the primary tumor and metastases are controlled by local treatment. Our purpose is to demonstrate, via a multicenter randomized phase III trial, that local treatment of metastatic sites with curative intent with SBRT associated of systemic standard of care treatment would improve the progression-free survival in patients with solid tumor (breast, prostate and non-small cell lung cancer) with up to 3 bone-only metastases compared to patients who received systemic standard of care treatment alone.

**Methods:**

This is an open-labeled randomized superiority multicenter phase III trial. Patients with up to 3 bone-only metastases will be randomized in a 1:1 ratio.between Arm A (Experimental group): Standard care of treatment & SBRT to all bone metastases, and Arm B (Control group): standard care of treatment.

For patients receiving SBRT, radiotherapy dose and fractionation depends on the site of the bone metastasis and the proximity to critical normal structures. This study aims to accrue a total of 196 patients within 4 years.

The primary endpoint is progression-free survival at 1 year, and secondary endpoints include Bone progression-free survival; Local control; Cancer-specific survival; Overall survival; Toxicity; Quality of life; Pain score analysis, Cost-utility analysis; Cost-effectiveness analysis and Budget impact analysis.

**Discussion:**

The expected benefit for the patient in the experimental arm is a longer expectancy of life without skeletal recurrence and the discomfort, pain and drastic reduction of mobility and handicap that the lack of local control of bone metastases eventually inflicts.

**Trials registration:**

ClinicalTrials.gov NCT03143322 Registered on May 8th 2017. Ongoing study

## Background

Cancer with bone metastases compared to other metastatic sites is considered as associated with a better prognosis, particularly for breast and prostate cancer despite a significant impact on the patient’s quality of life and autonomy. Many randomized controlled trials have demonstrated the efficacy of first-line palliative conventional radiotherapy for painful bone metastases [1–4]. The advent of novel imaging techniques allows an increasing an early detection and diagnosis of oligometastatic disease. In clinical practice the possibility to identify a few number of lesions, better defined recently by ASTRO, EORTC and ESTRO, it is considered an intermediate phase of tumor spread with limited metastatic capacity [5, 6].

Patients with oligometastatic disease have improved survival compared with those with high- volume metastatic disease. While systemic treatment is the standard of care. Stereotactic radiotherapy is a highly accurate technique initially developed for performing the radiosurgery of lesion in patients for whom it was deemed be to difficult to proceed to classical excision surgery. In the context of patients with oligo-metastatic cancer, high doses of radiation in stereotactic conditions can be safely delivered in bone metastases with increased probability of local control. Local control of bone metastasis is similar to than other localizations with a good control of pain [7, 8] and patients with oligometastasis had a longer survival with better local control for spine metastasis [9] and delay progression, and thereby postpone the need for further systemic treatment [10, 11].

In combination with curative-intent treatment to the primary tumor and systemic therapy, we hypothesize that an improved local control in the bone genuine de novo synchronous or metachronous oligometastatic disease would be associated with an increased Progression-Free Survival (PFS) and Overall Survival (OS).

Two ancillaries studies are associated:

- Biological ancillary study which search for pre-SBRT and follow-up markers (serum CTX and bone ALP) associated with skeletal-related events and bone progression disease.

- Economic ancillary study.

## Methods/design

This is an open-labeled randomized superiority multicentric phase III studyin French academic hospital. Patients will randomized in a 1:1 ratio between (Fig. 1):
Arm A (experimental group): Standard care of treatment (systemic treatment suitable for primary cancer) and SBRT to the bone metastases.Arm B (control group): Standard care of treatment (systemic treatment suitable for primary cancer) alone.

**Fig. 1 Fig1:**
[figure not shown]
Study Design. Footnotes: SBRT: Stereotactic Body radiation Therapy; CT Scan: Computed tomography Scann; PET: Positron Emission Tomography; SPECT-CT: Single Photon Emission Tomography-Computed Tomography

The sample size allows 2 stratification factors at randomization: date of metastases (synchronous vs metachronous) and primary tumor site (prostate vs breast vs lung). All patients will be randomized after completion of the primary tumor treatment for synchronous or metachronous metastasis. The randomization will be minimized by the following stratification factors. Minimization aims to ensure treatment arms are balanced with respect to predefined patient factors as well as for the number of patients in each group.

### Objectives

To assess the impact of SBRT on Progression Free Survival in patients with solid tumor with up to bone-only metastases, compare to patients who received standard of care treatment alone.

#### Primary endpoint

The primary endpoint is the 1-year PFS. Progression Free Survival PFS is defined as the time from randomization until the date of the first objective progression or death (whatever its cause in the absence of progression). Stereo-OS protocol will allow a specific focus on skeletal metastases and is thus expected to bring a clear-cut assessment of the added benefit of stereotactic radiotherapy on PFS.

#### Secondary endpoints

*The secondary endpoints are as follow:*
PFS at 2 and 3 years defined as the time from randomization until the date of the first objective progression or deathBone progression free-survival (BPFS) at 1 year defined as the time from the date of randomization to the date of documented bone progression at the level at the entire skeleton.Local control (LC) at 1 year defined as the time from the date of randomization to the date of a documented local event at the level of bone oligometastases presents at randomization.Cancer-specific survival (CSS) at 1, 2 and 3 years defined as the time from the date of randomization to the date of documented death from cancer or complication from the treatment.Overall survival (OS) at 1, 2 and 3 years defined as the time from the date of randomization to the date of documented death from any cause.Acute and late Toxicity at 1, 2 and 3 years assessed by the National Cancer Institute Common Toxicity Criteria (NCI CTC) version 4.0.Quality of Life assessed using self-administered questionnaires (EORTC-QLQ-C30, EORTC-QLQ-BM22, and EQ-5D-3L) [12–14].Pain score evaluated accordingly to Numeric Scale.The Cost- Utility /Cost-Effectiveness / Budget Impact analysis performed on QALYs (Quality-Adjusted Life Years) and ICERs (Incremental Cost-Effectiveness Ratios) calculation based on EQ-5D-3L questionnaire.

### Eligibility criteria

The inclusion criteria are as follow:
Patients older than 18 yearsGood general condition: WHO performance status ≤1Patients with histological proof of breast, non-small cell lung, or prostate cancerAbsence of co-morbidity contra-indicating radio-chemotherapy or surgeryPrimary tumor accessible to curative-intent treatment (surgery, chemoradiation…) for patients with synchronous metastases (ie randomization after treatment of primitive cancer)Patients with between 1 and 3 synchronous or metachronous bone metastases as defined by NaF-PET or conventional SPECT-CT scan and spinal MRI (if necessary) within 6 weeks before randomizationBones metastases treatable by SBRTPrimary cancer considered to be controlled or accessible to curative-intent treatment (surgery, chemoradiation…) in case of locoregional reccurence for metachronous bone oligo-metastatic diseaseWomen of childbearing potential and male patients must agree to use adequate contraception for the duration of study participation and up to 3 months following completion of therapy;Patients who have received the information sheet, dated and signed the informed consent formAffiliated to the social security system

The non-inclusion criteria are as follow:
Visceral metastases as defined by FDG-PET (or F-Choline-PET for prostate cancer) and cerebral CT or MRI performedPrevious systemic therapy for metastasis for patients with metachronous metastasis. Prostate and breast cancer patients remain eligible if hormonal treatment was initiated 6 months before enrollment.All bone metastasis requiring surgical treatment (spinal cord compression, fracture, …)More than 3 bone metastases as defined by NaF-PET or conventional SPECT-CT scan and spinal MRI (if spinal bone metastases on NaF-PET)Previous cancer within the 5 years before inclusion (except basal cell carcinoma of the skin, in situ carcinoma of the uterine cervix)Previous radiotherapy on bone metastasis (e.g: antalgic radiotherapy)Patient enrolled in another therapeutic trialPregnant women or breast feeding mothers,Hypersensitivity to the active substance (FDG and NaF or F-Choline for prostate cancer) or to any of the excipientsContraindication to MRI (in case of spinal metastases)Patients deprived of liberty or placed under the authority of a tutor. Patients with any psychological, familial, sociological or geographical condition potentially hampering compliance with the study protocol and follow-up schedule; those conditions should be discussed with the patient before registration in the trial. Patients unable to understand the purpose of the study (language, etc.).

### Evaluation and randomization

Prior to randomization, a complete history and physical examination is required. Histologically confirmation of malignancy is required, with metastatic disease detected on imaging.

The mechanism of implementing the allocation sequence (stratified randomization) is generated by computer. Clinical research assistant generate the allocation sequence and physician enroll and assign participant to intervention.

Patients must be restaged within 6 weeks before randomization, including brain CT or MRI and CT-TAP. For all patients with a suspicion of spinal bone metastases, a spinal MRI is mandatory.

The patients will also benefit from PET-CT exams before treatment. PET1 F-Choline, NaF and FDG are standard examinations for metastases staging; and PET2 FDG or F-Choline for evaluation. If NaF-PET cannot be done, patients will have a “conventional” biphosphonates SPECT-CT with a tomographic exploration from the vertex to mid-thigh in double or triple field instead.

Patients with prostate cancer are also required to have PSA blood test. A negative pregnancy is required for women of child-bearing age (Table 1).

**Table 1 Tab1:** Timeline and follow up of the study

	Screening	Randomization	Treatment	Follow up				
				M3	M6	Y1	Y2	Y3
**History & physical**	X		X	X	X	X	X	X
**Brain CT or MRI**	X				X	X	X	X
**TAP CT**	X				X	X	X	X
**FDG PET or F-Choline PET**	X					X		
**PET or SPECT-CT**	X					X		
**Spinal MRI (if spinal bone metastases)**	X				X	X		
**Mammography (breast cancer)**	X				X	X	X	X
**Histological confirmation**	X							
**Quality of Life**	X		X	X	X	X	X	X
**Toxicity Assessment**			X	X	X	X	X	X
**Pain Assessment**	X		X	X	X	X	X	X
**Economic Study**			X	X	X	X	X	X
**sCTX/ bALP Evaluation**	X		X	X	X	X		

*MRI* Magnetic Resonance Imaging; *TAP-CT* Computed tomography thorax-abdomen-pelvis; *FDG-PET* Fluorodesoxyglucose-Positron Emission Tomography; *F-Choline-PET* Fluor-Choline-Positron Emission Tomography; *PET* Positron Emission Tomography; *SPECT-CT* Single Photon Emission Tomography-Computed Tomography; *sCTX* serum C-Telopeptide cross-link of type 1 collagen; *bALP* bone ALkaline Phosphatase

The present research project will be developed for 48 months, during which specific milestones will be achieved and documented (Table 1).

### Interventions/treatments

#### Arm A

In case of SBRT, the acceptable regimens are 35 Gy / 7 fractions / 3 fractions per week or 27 Gy / 3 fractions / 3 fractions per week. An interval of at least 24 h should be kept between two consecutive fractions. Treatment planning and delivery will be performed using dedicated system. Strict quality assurance protocols will be implemented to ensure the accuracy in dose delivery.

All patients in Arm A will undergo planning CT simulation. CT simulation must be performed in the treatment position with adequate immobilization devices and the fiducials must be placed for stereotactic targeting if necessary. The use of intravenous contrast is recommended. Axial reconstructions will be required with slice thickness of around 1 mm. MRI, and PET if needed will be merged with CT simulation at the target volume on the simulation CT.

The Gross Tumor Volume (GTV) corresponds to the tumor volume visible on the simulation CT taking into account the information provided by the clinical examination and the other imaging modalities. (MRI is mandatory for spinal metastasis and experimental arm).

The Clinical Target Volume (CTV) corresponds to the macroscopic spread. Its limits are defined by Cox et al. for spine metastases or by CTV = GTV + 5 mm for the other bones [15].

The PTV is obtained by adding a margin around the CTV to take into account the set-up uncertainty during radiotherapy delivery with PTV = CTV + 2 mm. This margin can be reduced to 0 mm close to the spinal cord. Depending on the SBRT equipment, the beam aperture can be set to 2–3 mm beyond the CTV to provide adequate dose coverage. This margin can be reduced to 0–1 mm close to the spinal cord.

Prescription must be defined on 80% isodose or higher. At least 90% of the PTV should receive the prescribed dose. A coverage of < 90% of the PTV will be considered as Acceptable Deviation, and coverage of < 80% of the target volume as an unacceptable deviation. At least 90% of the GTV should receive the prescribed dose. A coverage of < 90% of the GTV will be considered as Acceptable Deviation, and coverage of < 80% of the target volume as an unacceptable deviation.

The organs at risk (OAR) of complication include all normal tissues located in the vicinity of the target or in the beams path. Specific dose-volumes constraints, defined by Timmermann, have to be respected to avoid unacceptable toxicity [16]. In the Experimental group with SBRT, all relevant OARs must be delineated. As for the spinal cord, two volumes have to be delineated: A “conventional” volume is delineated on the simulation CT after registration of MRI (T2-weighted and T1-weighted with contrast). The contour should be drawn at least 10 cm above and below the CTV, as recommended by NRG Oncology protocols. A “partial” volume is specific to the present study (Table 2). The contour drawn as above (“conventional” volume) extends 5–6 mm above and below the CTV [17].

**Table 2 Tab2:** OAR Constraints

	3D RT	SBRT 3 fractions	SBRT 5 fractions
**Spinal cord**	Dmax <45Gy	V18 ≤ 10% for « partial » volume	V23 ≤ 10%
	(standard fractionation)	V18 ≤ 0.35 cm^3^ for « conventional » volume	V23 ≤ 0.35 cm^3^
		V12 ≤ 1.2 cm^3^ for « conventional » volume	V14.5 ≤ 1.2 cm^3^
**Cauda equina**		V22.5 < 5 cm^3^	V30 < 5 cm^3^
		D2% < 24 Gy	D2% < 32 Gy
**Sacral plexus**		V22 < 3 cm^3^	V30 < 3 cm^3^

*3D RT* 3 Dimensional Radiation Therapy; *SBRT* Stereotactic Body radiation Therapy

For the others OAR not listed in Table 2, investigators must refer to AAPM Task Group 101 report. It is important to deliver as low a dose as possible in the organs at risk while assuring that a sufficient dose to the target volume is delivered.

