#### Arm B

In the Control group (without SBRT), palliative radiotherapy on bone metastases is allowed if necessary (pain, fracture, spinal cord compression …).

The acceptable regimens for patients in Arm1 are as follows as per consensus guidelines [18]:
30 Gy / 10 fractions / 5 fractions per week24 Gy / 6 fractions / 5 fractions per week20 Gy / 5 fractions / 5 fractions per week8 Gy / 1 fraction

The organs at risk are not delineated in the control group except for the spinal cord (Table 2).

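### One of the two permitted SBRT regimens (7 fractions) has no matching organ-at-risk limits in Table 2, and the table's 5-fraction SBRT column matches no permitted regimen

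*Protocol article*

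**What the plan says.** Under Interventions/treatments, Arm A, the protocol article names two SBRT regimens: "the acceptable regimens are 35 Gy / 7 fractions / 3 fractions per week" or "27 Gy / 3 fractions / 3 fractions per week".

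Table 2 (OAR Constraints), further on in the Arm A text, has three columns:
- 3D RT, which gives a spinal cord maximum only, marked "standard fractionation";
- "SBRT 3 fractions";
- "SBRT 5 fractions".

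The two SBRT columns give limits for spinal cord, cauda equina and sacral plexus. The text introducing the table makes dose-volume constraints mandatory and cites an outside publication for them. After the table it adds: "For the others OAR not listed in Table 2, investigators must refer to AAPM Task Group 101 report".

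The section on Quality Assurance of Radiation Therapy has a QA committee judge treatment plans on several criteria, dose constraints among them. It reviews each centre's first plan before radiotherapy starts and all SBRT-arm patients after treatment.

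**The concern.** The regimen list and the constraint table sit in the same section and should cover the same fractionations, but they do not. A centre planning the 7-fraction regimen finds no column for it in Table 2, and the table contains a column for an SBRT schedule that the article does not permit.

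The mismatch matters because the constraints are compulsory and are a stated criterion of plan review. The abstract also says that dose and fractionation are chosen by metastasis site and closeness to critical normal structures, so the choice of regimen is tied to the kind of structure that Table 2 covers. If the working documents carry the same mismatch, a planner could use the 5-fraction column unchanged, convert it, or go to another source. A reviewer scoring the plan could make a different choice. Whether a 7-fraction plan met the cord, cauda equina and sacral plexus limits would then depend on who was asked.

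**Working it through.** The article states no figure to reproduce here. The check sets the two parts of the Arm A section side by side.

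**Step 1: fraction numbers.**

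| SBRT fractions | Permitted regimen | Dose per fraction | Column in Table 2 |
|---|---|---|---|
| 3 | 27 Gy | 27 / 3 = 9 Gy | yes |
| 5 | none | – | yes |
| 7 | 35 Gy | 35 / 7 = 5 Gy | no |

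Permitted set {3, 7}; table set {3, 5}; overlap {3}. One of two permitted regimens has no column, and one of two SBRT columns has no regimen. The only 5-fraction schedule in the article is 20 Gy in 5 fractions for palliative radiotherapy in Arm B. That is not SBRT, so it does not explain a column headed as SBRT.

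**Step 2: does another column fill the gap?** The 3D RT column gives a cord limit only, tied to standard fractionation. It gives nothing for cauda equina or sacral plexus and is not an SBRT limit.

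**Step 3: does the AAPM referral fill it?** No. It applies to organs that Table 2 leaves out. Spinal cord, cauda equina and sacral plexus are all in the table, so by its own terms the referral does not reach them.

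**Step 4: could one column simply serve for another fraction number?** The table itself shows that the limits depend on the number of fractions:

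| Structure | 3 fractions | 5 fractions | Change in dose threshold |
|---|---|---|---|
| Spinal cord | V18 | V23 | 23 / 18 = 1.28, +28% |
| Spinal cord | V12 | V14.5 | 14.5 / 12 = 1.21, +21% |
| Cauda equina | V22.5 | V30 | 30 / 22.5 = 1.33, +33% |
| Cauda equina | D2% 24 Gy | D2% 32 Gy | 32 / 24 = 1.33, +33% |
| Sacral plexus | V22 | V30 | 30 / 22 = 1.36, +36% |

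Going from 3 to 5 fractions moves every dose threshold by 21% to 36%. The article gives no rule for carrying limits to another fraction number. These figures show only that the columns are not interchangeable; they do not indicate what a 7-fraction limit should be.

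**Step 5: extraction or condensation?** Neither accounts for it. Both places print explicit fraction numbers, the column headings are intact, and the numbers differ.

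**The case against.** The strongest reply is that this is a journal article condensed from a full protocol. Centres and the QA committee would work from that full document, whose constraint table is not shown. The article also cites an outside publication for the constraints, which may cover 7 fractions. This stands as a limit on the consequence: the article does not establish that centres actually lack limits for 7-fraction plans. It does not remove the inconsistency, because Table 2 as printed does not fit the regimen list as printed.

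A second reply is that central quality assurance reduces the risk. Each centre must pass a dummy run before it may include patients, its first plan is reviewed before treatment, and all SBRT patients are reviewed at the end. This is real control, but it does not supply the missing column, and the reviewers are themselves told to judge dose constraints.

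A reader might infer three stronger things that the document does not support.

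- *That toxicity results cannot be interpreted.* Toxicity is graded by NCI CTC version 4.0, independently of planning limits, and the data safety monitoring committee reviews it after 60 experimental-arm patients. Scoring of GTV and PTV coverage is also untouched.
- *That all of Arm A is affected.* With 1:1 allocation of 196 patients, 196 / 2 = 98 is only a ceiling. It would require every patient to receive 7 fractions and to have a lesion near one of the three structures. The Arm A text has a separate target-volume rule for non-spinal bones, so other sites are expected.
- *That the control arm has the same fault.* The Arm B text says: "The organs at risk are not delineated in the control group except for the spinal cord (Table 2"). Its palliative regimens total at most 30 Gy, against a 3D RT cord maximum of 45 Gy, which might suggest an empty limit. But the 45 Gy is stated for standard fractionation, while the Arm B regimens run from 30 / 10 = 3 Gy to 8 Gy per fraction, so unconverted totals are not comparable. Earlier cord dose from treatment of the primary is also possible, since only previous radiotherapy on bone metastases is excluded. A limit that one course seldom reaches is not a contradiction.

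**Conclusion.** The point holds as an inconsistency within the Arm A section. One of two permitted SBRT regimens has no limits in Table 2 for any of the three structures listed there, and one of two SBRT columns matches no permitted regimen. The AAPM referral does not close the gap. For patients planned with 7 fractions, compliance with the cord, cauda equina and sacral plexus constraints is unclear on the article's own terms. Their number cannot be derived, because the article gives no expected split between regimens or lesion sites.

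The textual mismatch is certain. Its practical effect rests on the assumption that neither the full protocol nor the cited constraint source supplies matching 7-fraction limits; neither was seen. The document does not show whether the regimen list or the table heading is in error. The sample size and the primary PFS comparison do not depend on this point. It should nevertheless be corrected, because it concerns mandatory limits for neural structures in the experimental arm.

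**What to change.** Reconcile the Arm A regimen list with Table 2 so that every permitted SBRT fractionation has matching limits for the listed structures and no SBRT column refers to a fractionation that is not permitted. The sponsor's radiotherapy leads must decide which entry is right; this review proposes no regimen or limit. First check whether the full protocol has the same mismatch. If it does, amend it, and in either case correct the article.

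Then inform the centres and the QA committee which limits apply, and re-check affected plans already reviewed against the reconciled table.

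The cost is a short protocol correction, a note to centres, and committee time for the re-check. No change to sample size, randomisation or the analysis follows.
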